#### Secondary outcomes

The incidence of recurrent IS and TIA.

The incidence of myocardial infarction.

The incidence of cardiovascular death.

The incidence of adverse events.

The incidence of all-cause mortality.

The mean of serum lipid levels [TG, TC, LDL-C, and high-density lipoprotein cholesterol (HDL-C)] for 36 months with at least 3 measurements.

The variability of serum lipid levels (TG, TC, LDL-C, and HDL-C) for 36 months with at least 3 measurements.

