**Discussion:**

The primary hypothesis of this study is that an excessive reduction in serum lipid levels by an intensive statin therapy in AIS patients with CMBs can increase the risk of intracranial hemorrhage. This study will shed light on new clinical decisions regarding the long-term serum lipid management in these patients with dilemma in clinical practice.

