Statins have been widely used for secondary prevention of IS. The Stroke Prevention by Aggressive Reduction in Cholesterol Levels (SPARCL) study had proposed that the reduction in the risk of IS was primarily related to the extent to which low-density lipoprotein cholesterol (LDL-C) levels are lowered instead of statin use (17). It was the first to demonstrate that 80 mg of atorvastatin per day reduced the overall incidence of strokes and cardiovascular events in patients with recent stroke or transient ischemic stroke (TIA) and without known coronary heart disease (17). However, the correlation between statin use of an intensive dose and ICH risk has not been elucidated so far (18–20). A recent meta-analysis on intensive LDL-C-lowering statin-based therapy also revealed an increased risk of ICH related to high-dose statins (17, 21), while other studies did not show the similar conclusions that statin use (22) or intensive reduction of LDL-C (23) increased the ICH risk. More importantly, none of these previous studies have explored the relationship between intensive statin therapy and hemorrhage risk from the perspective of CMBs.

However, it is worth noting that low levels of serum triglycerides (TG), total cholesterol (TC), and LDL-C have been proved to be significantly associated with increased risks of hemorrhagic stroke (HS) and CMBs (17, 19, 24). Thus, the risk of hemorrhagic events appears to depend on the reduction extent and degree of blood lipid levels rather than on statin use *per se* (17–22, 24). Unfortunately, the current international guidelines on lipid modification are all committed to emphasize the intensive reduction for LDL-C to prevent ischemic events, with no instructions on a more propriate target range to balance the prevention of ischemic stroke recurrence and the prevention of hemorrhagic events, especially for patients requiring high-dose statin treatment. Therefore, it is of great scientific and practical significance to conduct prospective studies to reveal the clinical and neuroimaging characteristics of CMBs in acute ischemic stroke (AIS) patients, and to explore the correlation between intensive lipid-lowering therapy and hemorrhage risk.

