### Follow-up

Detailed follow-up schedules and procedures are provided in Figure 1. Baseline characteristics, SWI and clinical laboratory tests will be obtained at enrollment. The following assessments will be performed at 1 month and annually follow-up: blood tests, SWI, study compliance, concomitant medication, adverse events, and withdrawal criteria. As it is not clear whether participants in this study would benefit more from following current guidelines or moderately relaxed lipid management targets. No further interventions which might violate the study protocol should be taken (such as suggesting withdrawal from the study or adjusting the treatment plan, etc.) if it is found that the serum lipid levels of the participants do not meet the current guidelines either for both groups. But the participants' doctor should be informed to strictly monitor their lipid levels and clinical conditions.

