## Discussion

CMBs have been identified as a potential neuroimaging biomarker of SCVD that are prone to spontaneous ICH (10). In IS cohorts, CMBs were found to be associated with the risks of both subsequent ICH and recurrent IS, while the relative risk of subsequent ICH seemed to rise more steeply than that of IS as the burden of CMBs increased (13, 14). This suggests that in the secondary prevention of IS, we need to pay attention to the risk of hemorrhagic events in addition to the benefit of ischemic events, especially for patients with CMBs.

At present, as a choice for secondary prevention of arteriosclerotic cardiovascular disease (ASCVD) patients and primary prevention of patients with elevated risk of ASCVD, statins have been widely used in clinical practice. The SPARCL study was the first to demonstrate that 80 mg of atorvastatin per day reduced the overall incidence of strokes and cardiovascular events in patients with recent stroke or TIA and without known coronary heart disease (17). But this study also revealed an increased risk of ICH related to high-dose statins (17). A recent meta-analysis showed that serum levels of major lipids (TC, TG, and LDL) were negatively correlated with CMBs, but there was no sufficient evidence for statin use as a risk factor for CMBs (19). Thus, it is reasonable to speculate that the risk of statin-related hemorrhage appears to depend on the extent to which certain serum lipid levels are reduced, rather than on statin use *per se*. Taken together, these findings present a paradoxical problem: high-dose statins have a protective effect on IS recurrence but are likely to be harmful for hemorrhage risk, including HS and CMBs.

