In addition, in the secondary prevention of IS, national guidelines around the world delineate different lipid regulation criteria for different baseline conditions, emphasizing the use of high-intensity or maximum tolerated doses of statins to achieve serum LDL-C < 1.8 mmol/L (70 mg/dl) and/or a ≥50% reduction from baseline in those most likely to benefit (25, 26). However, current clinical studies and practice guidelines have failed to suggest lower limits for lipid management goals. Several studies have confirmed that lower serum TG, TC, and LDL-C levels increased the risk of CMBs (17, 19, 24, 27), and the presence of CMBs was associated with increased subsequent ICH risk and poor functional prognosis in patients with AIS (28). These studies suggest that unlimited reduction of serum major lipid levels, mainly LDL-C, is likely to be detrimental in the secondary prevention of IS, especially in IS with CMBs. Therefore, further studies are urgently needed to explore the safe lower limits of lipid management goals in IS with CMBs.

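### The hypothesis is about how far lipids are reduced, but the stated lipid outcomes and analyses use only levels and variability, never change from enrolment

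*Protocol article*

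**What the plan says.** The Discussion paragraph of the abstract gives the primary hypothesis: "an excessive reduction in serum lipid levels by an intensive statin therapy in AIS patients with CMBs can increase the risk of intracranial hemorrhage". The Introduction gives the rationale: "the risk of hemorrhagic events appears to depend on the reduction extent and degree of blood lipid levels rather than on statin use". The main Discussion repeats it: "the risk of statin-related hemorrhage appears to depend on the extent to which certain serum lipid levels are reduced". It also cites a guideline target expressed partly as a relative fall: "and/or a ≥50% reduction from baseline in those most likely to benefit".

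Secondary outcomes lists two lipid measures. One is "The mean of serum lipid levels [TG, TC, LDL-C, and high-density lipoprotein cholesterol (HDL-C)] for 36 months with at least 3 measurements"; the other is "The variability of serum lipid levels (TG, TC, LDL-C, and HDL-C) for 36 months with at least 3 measurements". Statistical analysis compares both between arms by Student t-test or Wilcoxon rank-sum test. It then plans a generalized linear mixed model relating the degree of microbleeds to lipid levels over time.

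On sampling, Follow-up says: "Baseline characteristics, SWI and clinical laboratory tests will be obtained at enrollment". Blood tests follow at 1 month and then annually. Table 1 allows entry up to 14 days after the stroke. Its exclusion 15 removes patients who must take a different statin or another lipid-lowering drug. No listed criterion removes a patient already taking atorvastatin.

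**The concern.** A reduction needs a starting point and an end point. The mean over follow-up describes where lipids settled, and the variability describes how much they moved around. Neither says how far they fell. The mixed model, as described, also works with levels. The quantity that the hypothesis names is therefore not a defined outcome, and it is not the exposure in any stated analysis.

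The starting point needs care too. If some patients are on atorvastatin when the enrolment sample is drawn, part of their reduction has already happened. Their change from enrolment then means something different from that of untreated entrants.

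At stake is interpretation. The trial can show whether the assigned dose affects bleeding. Its stated rationale goes further and attributes the risk to the extent of reduction rather than to statin use as such. The stated analyses do not address that in a prespecified way.

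**Working it through.** **Plan's own figures.** The article gives no figure for lipid reduction, so there is none to reproduce on this point. Its one computed figure is the sample size. With 25.2% versus 12.0%, two-sided 5% and 80% power, the pooled-variance formula gives 136 per arm against the stated 137. Then 137/0.8 = 171.25, rounded up to 172 per arm, or 344 in total. The sample size reproduces and has no bearing on this point.

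**Step 1: does the on-study mean fix the reduction?** Reduction = 1 − (on-study level / untreated level). Take an on-study LDL-C of 1.8 mmol/L and assumed untreated values:

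- 1 − 1.8/2.4 = 25%
- 1 − 1.8/3.0 = 40%
- 1 − 1.8/3.6 = 50%
- 1 − 1.8/4.2 = 57%

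The same mean is compatible with very different reductions in individual patients.

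**Step 2: what does change from enrolment show in a patient already treated?** Let r1 be the reduction from the untreated level on study, and r0 the part already achieved at the enrolment sample. Apparent reduction = 1 − (1 − r1)/(1 − r0). The values of r1 and r0 are assumptions, because the article gives none.

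| r1 | r0 = 0 | 10% | 20% | 30% | 40% |
|---|---|---|---|---|---|
| 50% | 50% | 44% | 38% | 29% | 17% |
| 40% | 40% | 33% | 25% | 14% | 0% |

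**Step 3: what happens to the arm averages?** Assume reductions from the untreated level of 50% on 80 mg and 40% on 20 mg, with a fraction f of patients entering on 20 mg. Such a patient shows 1 − 0.50/0.60 = 16.7% on 80 mg and 0% on 20 mg. Arm means are (1 − f) × 0.50 + f × 0.167 and (1 − f) × 0.40.

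| f | 80 mg | 20 mg | difference |
|---|---|---|---|
| 0% | 50% | 40% | 10 points |
| 10% | 47% | 36% | about 11 |
| 30% | 40% | 28% | 12 |
| 50% | 33% | 20% | about 13 |

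The apparent size of the reduction is clearly distorted within each arm. The contrast between arms moves little.

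**Step 4: what happens to the planned mean?** Under the same assumptions, on-study LDL-C is 0.50 of the untreated level on 80 mg and 0.60 on 20 mg, whether or not the patient entered on a statin. The planned between-arm comparison of means is not distorted by prior use.

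**Step 5: what does the unadjusted test give up?** Adjusting follow-up LDL-C for the enrolment value cuts its residual variance by about r². At an assumed correlation of 0.4 to 0.6, that is 0.4² = 16% to 0.6² = 36%.

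**The case against.** The strongest case on the other side has four parts.

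First, a reader might infer that the reduction cannot be derived at all. The article does not support that. It takes laboratory tests at enrolment and blood tests throughout follow-up, so a change from enrolment can be computed. This assumes that the enrolment tests include lipids, which the text does not name; Figure 1 may show it but is not available. For patients off statins at that sample, the change is a true on-treatment reduction.

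Second, a reader might infer that the main result is compromised. It is not. The abstract's aim and the sample size section frame the confirmatory test as high-dose against low-dose arm, and that test needs no measured reduction. Randomisation also balances untreated level and prior statin use in expectation. The between-arm difference in mean lipids therefore estimates the difference in absolute reduction.

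Third, part of the rationale concerns achieved level. The abstract's background speaks of low serum lipids, and the Discussion seeks a safe lower limit for lipid targets. The on-study mean and the mixed model on levels address that directly.

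Fourth, covariates and prior medication are often left to the analysis plan, and a medication history may already be collected.

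The first three stand and set the limits of the point. The fourth stands only in part: the article does list its lipid outcomes and name their tests, and those named items contain no measure of change. It would also be too much to say that the lipid check against guidelines in Follow-up misfires. That section states no percentage criterion and calls for no change of treatment.

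**Conclusion.** The point holds in a limited form. The hypothesis and rationale name the extent of reduction, while the stated outcomes and analyses use mean, variability and level, with an unadjusted between-arm test. Change from enrolment is not defined as an outcome or an exposure. If it were computed later without regard to prior treatment, it would understate the reduction from the untreated level in patients who entered on atorvastatin.

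On the assumed 50% and 40% reductions, the understatement in a patient entering on 20 mg is from 50% to about 17% on 80 mg, and from 40% to 0% on 20 mg. Across an arm it depends on the share of such patients, which the article does not give. With 10% to 50% pretreated, the apparent means are 47% to 33% on 80 mg and 36% to 20% on 20 mg.

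The primary comparison and the between-arm lipid contrast remain valid. The cost falls on the mechanistic conclusion: as written, the trial would have little prespecified basis for saying that the size of the reduction, as distinct from assigned dose or achieved level, drives bleeding.

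**What to change.** 1. In Statistical analysis, replace the unadjusted lipid comparison with a model for follow-up LDL-C by arm, adjusted for the enrolment value and for statin use at the enrolment sample (none, or which statin and dose). With the enrolment value as a covariate, the arm effect is the same for follow-up level and for absolute change, so this comparison does not rest on percentage change, the measure most distorted by prior use.
2. In Secondary outcomes, add change in LDL-C from enrolment at months 1, 12, 24 and 36, reported separately for entrants on and off a statin.
3. In the planned mixed model for microbleed degree, add that change as an exposure alongside achieved level, again separately by statin use at entry. Label the result a non-randomised, exploratory association: comparing percentage change between arms does not by itself link reduction to haemorrhage. Absolute change is level minus enrolment value, so a model holding both terms carries the same information as one with level and enrolment value; interpret the coefficients accordingly.

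The cost is small: one medication-history field if it is not already collected, and one more secondary analysis. No new samples are needed, provided the enrolment tests include lipids. Eligibility, allocation and treatment are untouched.

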### Sample size estimates

Sample size calculations were based on the primary outcomes (the incidence of ICH). All participants are expected to be enrolled for 1 year and followed for 36 months. It will be tested whether the high-dose statin arm suffers a higher risk of hemorrhage than the low-dose statin arm in terms of the primary outcomes for 36 months. According to the SPARCL trial (the incidence of ICH: 25.2 vs. 12.0% in high-dose statin arm vs. low-dose statin arm with 4.9 years of mean follow-up duration) (17). The sample size was calculated by PASS software (version 15.0) with a two-sided type I error of 5% (α = 0.05) and 80% power, a sample size of 137 patients in each arm is required (total 274 patients). Assuming around 20% loss to follow-up, a total of 344 patients will be randomized.

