**Aim:**

The Intracranial **H**emorrhage **R**isk of Intensive **S**tatin **T**herapy in Patients with **A**cute **I**schemic **S**troke combined with **C**erebral **M**icrobleeds (**CHRISTMAS**) trial evaluates the risk of intracranial hemorrhage (i.e., HS and CMBs) of high-dose statin therapy in patients with AIS combined with CMBs.

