## Introduction

Cerebral microbleeds (CMBs) are a crucial radiological marker of cerebral small vessel disease (CSVD) (1) to illustrate the micropathology of perivascular hemosiderin deposition corresponding to past small foci of bleeding (2). The prevalence of CMBs increases with age and exceeds 20% in community population over 60 years old (3, 4). More importantly, CMBs are also a common comorbidity of stroke, brain trauma, Alzheimer's disease, and cerebral amyloid angiopathy (5, 6), and are associated with cognitive impairment, psychiatric symptoms, and decline of daily living ability (7).

CMBs have been identified to be indicative of bleeding-prone microangiopathy for their dynamical accumulation over time, with the burden (presence and number) of baseline CMBs predicting the development of new CMBs in both deep and lobar regions, and may predict spontaneous intracranial hemorrhage (ICH) (8–12). These pieces of evidence have suggested an important link between the presence of CMBs and future macrobleeding. However, CMBs have also been demonstrated in approximately one-third of patients with ischemic stroke (IS), that are associated with an increased risk of recurrent IS, symptomatic ICH and death (13). As the burden of CMBs in IS patients increased, the relative and absolute risk ratios for ICH increase steeply, although the absolute incidence of recurrent IS is consistently higher than that of ICH (13–16). Therefore, it raises clinical dilemmas, particularly regarding the safety of secondary prevention treatment of IS with concomitant presence of CMBs.

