### Outcomes

#### Primary outcomes

The trial has co-primary outcome, namely, hemorrhage risk.

The first part is the incidence of HS confirmed by brain computed tomography (CT) or magnetic resonance imaging (MRI).

The second part is the changes in degree of CMBs until the end of 36 month follow-up.

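### The 80% power claim uses 4.9-year rates for a 36-month endpoint; scaled to 36 months, power is about 56–61%, and the rates and the sized outcome need checking

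*Protocol article*

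**What the plan says.** **Planning rates.** Sample size estimates takes from the source trial "the incidence of ICH: 25.2 vs. 12.0% in high-dose statin arm vs. low-dose statin arm", "with 4.9 years of mean follow-up duration". With a "two-sided type I error of 5"% and 80% power it arrives at 137 per arm (274 in total), raised to 344 for about 20% loss.

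**Time frame.** The same paragraph states: "All participants are expected to be enrolled for 1 year and followed for 36 months". It says that the arms will be compared on the primary outcomes over 36 months.

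**Outcome.** The paragraph names the incidence of ICH as the sized outcome. Primary outcomes lists two parts. On the first it says: "The first part is the incidence of HS confirmed by brain computed tomography (CT) or magnetic resonance imaging (MRI"). The second is change in degree of CMBs. The Aim in the abstract says that the trial "evaluates the risk of intracranial hemorrhage (i.e., HS and CMBs) of high-dose statin therapy", so there intracranial hemorrhage covers both parts. The Introduction abbreviates spontaneous intracranial hemorrhage as ICH.

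**The source trial elsewhere.** The Introduction reports that "80 mg of atorvastatin per day reduced the overall incidence of strokes and cardiovascular events in patients with recent stroke" or transient ischemic attack. The Discussion repeats this and adds that ICH risk rose on high-dose statin. Neither gives another ICH rate.

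**The concern.** Three things in one paragraph weaken the stated power.

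- **Time frame.** Fewer events accrue in 36 months than in 4.9 years, so the absolute difference between arms shrinks and power falls with it.
- **Size of the rates.** A quarter of the high-dose arm with ICH, in a trial said to have had fewer strokes overall on that dose, would need a large offsetting fall in other strokes. That raises the question of what 25.2% and 12.0% are percentages of.
- **Outcome.** A reader cannot tell whether the 80% applies to HS, to CMB change, or to the two together.

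At stake is the trial's main safety question. If HS is much rarer than planned, a non-significant HS comparison is the likely result even if high-dose treatment doubles the risk, and it could be misread as reassurance.

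**Working it through.** **Inputs (Sample size estimates).** p1 = 0.252, p2 = 0.120, mean source follow-up 4.9 years, trial follow-up 3 years, two-sided α = 0.05 (z = 1.960), power 80% (z = 0.842), 137 evaluable per arm, 20% loss.

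**Step 1: reproduce the plan's figure.** With p̄ = (p1 + p2)/2,

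n = [1.960·√(2p̄(1−p̄)) + 0.842·√(p1(1−p1) + p2(1−p2))]² / (p1 − p2)²

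Here p̄ = 0.186 and the two roots are 0.5503 and 0.5423, so n = (1.0785 + 0.4564)² / 0.132² ≈ 135.2, that is 136 per arm (stated: 137). Power at 137 is 80.5%. Loss: 137/0.8 = 171.25, so 172 per arm and 344 in total. The arithmetic is sound.

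**Step 2: scale the rates to 36 months.** The ratio of follow-up times is 3/4.9 = 0.612.

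- Constant hazard: 1 − 0.748^0.612 = 16.3%; 1 − 0.880^0.612 = 7.5%.
- Linear: 25.2 × 0.612 = 15.4%; 12.0 × 0.612 = 7.3%.

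**Step 3: power at 137 per arm, same formula.**

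| Rates used | Power at 137 per arm | n per arm for 80% |
|---|---|---|
| 25.2% vs 12.0% (as stated) | 80.5% | 136 |
| 16.3% vs 7.5% (constant hazard) | 61% | 214 |
| 15.4% vs 7.3% (linear) | 56% | 242 |

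After 20% loss, 214 per arm becomes 268 (214/0.8 = 267.5), or 536 in total. With Fisher's exact test, which the plan also allows, power is about 77% at the stated rates and about 55% at the constant-hazard rates.

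**Step 4: are the rates plausible as per-patient risks?** Count each patient once: any stroke = ICH + non-ICH stroke only. If any stroke was less frequent on 80 mg, then

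non-ICH (comparator) − non-ICH (80 mg) > 25.2 − 12.0 = 13.2 percentage points.

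A fall of that size is possible but hard to believe. This step assumes that ICH counts as stroke and that the percentages are of patients randomized.

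**Step 5: sensitivity to the HS rate.** The low-dose 36-month rates below are assumptions, not figures from the documents. The ratio is held at 25.2/12.0 = 2.1, with 137 per arm.

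| Low vs high dose | Power | n per arm for 80% |
|---|---|---|
| 1% vs 2.1% | about 10% | 1,979 |
| 2% vs 4.2% | 16–18% | 974 |
| 3% vs 6.3% | 25% | 638 |
| 5% vs 10.5% | 40% | 370 |

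At 2%, exact enumeration of the chi-square test gives 16% and the normal approximation 18%. Fisher's test gives about 2%, 9%, 16% and 31% down the table.

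**The case against.** **The calculation is correct for its inputs.** This stands. The defect lies in the inputs, so it would be wrong to say that the sample size was miscalculated or has no basis at all.

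**The rates are not contradicted.** This stands too. A reader might infer that 25.2% vs 12.0% cannot be reconciled with the rest of the article. The article gives no second ICH rate for the source trial, and its statement that ICH risk rose agrees in direction. A reader might go further and derive that over half of the 80 mg arm had a stroke, because "the absolute incidence of recurrent IS is consistently higher than that of ICH". That sentence describes other cohorts of ischemic stroke patients as CMB burden rises, and the step also assumes little overlap between patients with each stroke type, which the article does not state. That the figures are really a share of stroke events is likewise a guess about a publication not at hand.

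**ICH and HS overlap.** For HS the mismatch is mostly one of wording, so it would be too strong to say that the sized outcome is not tested. For CMB change the gap is substantive.

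**This population may bleed more.** Every participant has CMBs, and the article says ICH risk climbs with CMB burden. Rates above the scaled ones are therefore possible, but the plan does not make that argument or give a figure for it.

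**The interim analysis reviews event incidence.** Statistical analysis does schedule this, but the review does not correct the stated power, and it would compare observed incidence with an unscaled benchmark.

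**Conclusion.** Wrong as written. On the article's own figures, power for a 36-month comparison with 137 evaluable per arm is about 56–61%, not 80%. This assumes that the rates are per-patient risks accrued at a constant hazard or linearly over 4.9 years, and that each participant is followed for 36 months.

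The rates are implausible as per-patient ICH risks, but only the cited publication can settle their unit and denominator. If the true low-dose HS risk were between 1% and 5%, power would be about 10% to 40%; that range is an assumption. The sized outcome needs one clear name, and the paragraph shows no planning assumption for CMB change.

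**What to change.** 1. Check in the cited trial the numerator and denominator (patients randomized) behind 25.2% and 12.0%.
2. Restate the planning rates as per-patient HS risks at 36 months, and say how they were scaled.
3. Name HS, not ICH, as the outcome that the sample size serves, and say what planning assumption, if any, supports the CMB co-primary outcome.
4. Replace the 80% claim with the resulting power at 137 per arm, beside a sensitivity table such as the one above.
5. If HS power proves low, report HS as an estimate with a confidence interval, and state in advance that a null result will not be read as evidence of safety.

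The cost is one source check and one rewritten paragraph. No patients are added; the downside is a less favorable power statement.

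### The sample size enters haemorrhage incidences from a mean of 4.9 years unscaled into a 36-month comparison, so the stated 80% power does not follow from the plan's own inputs

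*Protocol article*

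**What the plan says.** All the relevant text is in the protocol article, Sample size estimates.

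- Outcome used for sizing: "Sample size calculations were based on the primary outcomes (the incidence of ICH".
- Planning rates and their time base: "25.2 vs. 12.0% in high-dose statin arm vs. low-dose statin arm with 4.9 years of mean follow-up duration".
- Follow-up in this trial: "All participants are expected to be enrolled for 1 year and followed for 36 months".
- Horizon of the test: whether "the high-dose statin arm suffers a higher risk of hemorrhage than the low-dose statin arm in terms of the primary outcomes for 36 months".
- Error rates: "two-sided type I error of 5% (α = 0.05) and 80% power".
- Result: "a sample size of 137 patients in each arm is required (total 274 patients", and then "Assuming around 20% loss to follow-up, a total of 344 patients will be randomized".

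Under Statistical analysis, haemorrhagic stroke is compared first by chi-square or Fisher's exact test, then by Kaplan-Meier and log-rank. The primary analysis is by intention to treat.

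**The concern.** A cumulative incidence grows with follow-up. A risk that took an average of 4.9 years to build up cannot serve as the risk at 3 years unless nearly all the events come early or the new population bleeds more often. The section states both time spans within a few lines and neither converts the rates nor argues that they carry over.

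Haemorrhage incidence is the only outcome used to size the trial, and the hypothesis is one of harm. If the stated power is too high, the chance of missing the assumed excess is larger than the 20% that a reader would take from the article. A non-significant difference could then be given more weight as evidence of safety than the design supports.

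**Working it through.** **1. Reproduce the stated size.** Inputs from Sample size estimates: p1 = 0.252, p2 = 0.120, two-sided α = 0.05 (z = 1.960), power 80% (z = 0.842), 1:1 allocation. With p̄ = 0.186, the pooled two-proportion formula is

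n = [1.960·√(2p̄(1−p̄)) + 0.842·√(p1(1−p1) + p2(1−p2))]² / (p1−p2)²

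= [1.960 × 0.5503 + 0.842 × 0.5423]² / 0.132² = 135.2, so 136 per arm.

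The article states 137, at which power is 80.5%. Other variants fit less well: 133 unpooled, 150 with continuity correction, 107 one-sided. Allowance for loss: 137/0.8 = 171.25, so 172 per arm and 344 in total, as stated. The arithmetic is therefore sound, and it shows that 25.2% and 12.0% went in unchanged.

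**2. Put the rates on a 36-month basis.** Assume constant hazards, and read the given figures as cumulative incidences at 4.9 years. The exponent is 3/4.9 = 0.612.

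- High dose: 1 − (1 − 0.252)^0.612 = 16.3%
- Low dose: 1 − (1 − 0.120)^0.612 = 7.5%

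The hazard ratio is unchanged: ln(0.748)/ln(0.880) = 2.27.

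**3. Power at 137 evaluable per arm.** The difference is 0.0876 and p̄ = 0.1191.

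z = [0.0876·√137 − 1.960 × 0.4580] / 0.4538 = 0.281, so power = 61.1%.

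**4. How far this depends on the choices made.**

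| Case | Power |
|---|---|
| Constant hazard, pooled z, 137 per arm | 61% |
| Same, exact power of the chi-square test | 62% |
| Same, chi-square with continuity correction | 55% |
| Linear scaling (0.612 × each rate: 15.4% vs 7.3%), pooled z | 56% |
| Log-rank, 137 × (0.163 + 0.075) ≈ 33 events, hazard ratio 2.27 | 65% |
| Log-rank, 172 per arm, exponential loss reaching 20% at 36 months, about 37 events | 70% |
| Pooled z, all 172 per arm evaluable | 71% |

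One more favourable combination is left out of the range because it contradicts the planned 20% loss. A log-rank test with no loss at all would have 172 × 0.238 ≈ 41 events and 75% power, still short of 80%.

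**5. What would restore 80%.** Each case below uses the pooled z test at 137 per arm.

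- *Early events.* If 80%, 90% or 95% of the 4.9-year cumulative hazard fell within 36 months, power would be 72%, 77% or 79%. Essentially all of it would have to fall there.
- *Higher risk in this population.* With the hazard ratio held and hazards 1.25 or 1.5 times the source trial's, power is 70% or 77%. A multiplier of 4.9/3 = 1.63 returns exactly 25.2% and 12.0% at 36 months.
- *Larger effect.* Against 7.5% in the low-dose arm, 80% power needs about 19.0% in the high-dose arm.

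**The case against.** The strongest reply is that 61% is itself conditional. The article does not give the shape of the hazard. Nor does it show that the source trial's risk applies here. The Introduction describes that trial as one in recent stroke or TIA without known coronary heart disease and mentions no selection for microbleeds, whereas every patient in this trial has them. The Introduction and Discussion both say that bleeding risk rises with microbleed burden. A higher hazard would offset some or all of the shorter follow-up. In addition, under intention to treat with a log-rank test, patients lost to follow-up contribute until they are censored, so counting only 137 per arm is on the cautious side.

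These arguments stand, and they rule out a flat statement that the trial's true power is 61%. They do not rescue the stated 80%. The sample size section does not invoke the higher risk of patients with microbleeds, gives no multiplier and makes no claim about early events. An offset that is not written down cannot support the figure.

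Two further replies have some weight. The interim analysis will look at the assumptions about event incidence, but that later look does not correct the power now stated. The plan also promises 95% confidence intervals, which will show what the data exclude whatever the planned power was. That limits the risk of misreading a null result but does not remove it.

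**Conclusion.** The point holds as a mismatch between the planning rates and the time horizon, both stated in the same section. The calculation was done correctly on an input that does not fit the comparison. On the plan's own figures, with constant hazards and the source trial's level of risk, power for haemorrhage is about 61% at 137 evaluable per arm and about 55–71% across the tests, scalings and loss assumptions in the table. The exact value depends on those assumptions. The direction does not, unless nearly all the cited risk falls within 36 months or this population's hazards are about 1.63 times the source trial's.

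A reader might go further and infer that the trial is certainly underpowered, or that it must enrol more patients. The documents support neither. The bleeding rate in patients with microbleeds over 36 months is not given and may be higher than the scaled figures. The point also concerns only the haemorrhage part of the co-primary outcome, because change in microbleeds was not used for sizing.

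**What to change.** Revise the sample size paragraph in one of two ways.

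1. Restate the planning incidences at 36 months (16.3% versus 7.5%) with the constant-hazard assumption shown. Replace the 80% claim with about 61% at 137 evaluable per arm and a range of about 55–71%. Equivalently, say that 80% power holds only for about 19.0% versus 7.5% at 36 months.
2. If 25.2% and 12.0% are intended as 36-month risks because all patients have microbleeds, say so, state that this implies hazards about 1.63 times those of the source trial, and give the evidence for it.

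Neither route changes enrolment or follow-up. The cost is one rewritten paragraph and, under the first route, a less favourable stated power.
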